#### Assignment of intervention

##### Allocation

At the end of Visit 2- subjects will be randomized at a ratio of 1:1:1 to each study group and stratified based on gender. Randomization will be conducted by a randomization software (computer generated random numbers) [34]. A third party who is not aware of research protocol will allocate patients into the study groups a priori to first recruitment using the randomization software and will create and keep the allocation list. Once recruitment for a particular baseline day and all baseline measurements are finished, a mediator in the IEMH (secretary) will contact the third party to reveal the allocations of the participants recruited and examined so far (allocation concealment).

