### Statistical methods

#### Sample size

The sample size calculation is based on the assumption that the mean difference in weight after 10 weeks between the empagliflozin arm and the CRT arm will be − 3.2 Kg. We assumed that the weight will not change in the CRT only group (body composition may change) and, based on the literature, that empagliflozin treatment causes a reduction in weight of ≈ 3–3.5 Kg. For 80% power and significance level of 5% each arm should include 40 subjects (*n* = 120 total). Another calculation was based on ANOVA for the comparison of three groups. We assumed that body fat % at the end of study will be 37, 36 and 40% for the diet, drug and CRT arms, respectively, with a 6% SD in each group. These assumptions are based on unpublished data obtained in a pilot study conducted in the IEMH. Assuming an attrition of ~ 10% we intend to recruit 120 up to 140 participants. Power calculations were performed using the G*Power Statistical Power Analyses for Windows [53].

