##### Baseline comparisons

To test differences in continuous variables between the study groups the one-way analysis of variance (ANOVA) test will be performed (or Kruskal–Wallis one-way analysis of variance when normal distribution is rejected). For comparison of dichotomous or categorical variables the Chi square test will be performed.

The primary endpoints (% change in LBM and change in weight) will be analyzed using the analysis of covariance (ANCOVA) after 10 weeks and after 20 weeks (for diet and drug arms only) including several factors and covariates. Table 2 indicates the list of covariates and factors. Table 3 indicates the different outcomes and appropriate statistical method.

**Table 2 Tab2:** List of potential covariates and factors (partial list)

Factor or covariate	Type	Defined as
Treatment	Factor	SGLT2 inhibitor, diet, CRT
GLP1 agonists	Factor	Yes, no
Baseline body weight/ BMI	Covariate	–
HbA1c (%)	Covariate	–
Caloric consumption (Kcal)	Covariate	–
Resting metabolic rate (Kcal)	Covariate	–
Body fat %	Covariate	–
Strength (kg)	Covariate	–
Frailty or sarcopenia status	Factor	Frail or sarcopenic, pre-frail or pre sarcopenic and robust

*Abbreviations*: *BMI* Body Mass Index, *CRT* Circuit Resistance Training, *GLP-1* Glucagon-Like Peptide-1, *HbA1c* Hemoglobin A1C

**Table 3 Tab3:** The different outcomes and appropriate statistical method (partial list)

	Endpoint type	Statistical method
Primary outcome		
Change in body weight (%) from baseline to 10 weeks or to 20 weeks	Continuous	ANCOVA
Change in % lean body mass from baseline to 10 weeks or to 20 weeks	Continuous	ANCOVA
Proportion of participants having lost ≥2.5% at week 10 and 20	Binary	Logistic regression
Secondary outcomes		
Change in waist circumference from baseline to 10 weeks or to 20 weeks	Continuous	ANCOVA
Change in FPG and HB1Ac from baseline to 10 weeks or to 20 weeks	Continuous	ANCOVA
Change in sarcopenia and frailty status (improved vs. not improved; change from one level to the other) at week 10 and 20	Binary	Logistic regression
Change in strength and other functional abilities from baseline to 10 weeks or to 20 weeks	Continuous	ANCOVA
Change in systolic blood pressure from baseline to 10 weeks or to 20 weeks	Continuous	ANCOVA
Change in quality of life (improved vs. not improved; change from one level to the other) at week 10 and 20	Binary	Logistic regression

*Abbreviations*: *ANCOVA* Analysis of Covariance, *FPG* Fasting Plasma Glucose, *HbA1c* Hemoglobin A1C

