Primary analysis will be intent to treat analysis. It will include all patients that had been randomized, started protocol and reached the end of the trial examinations (or last observation available will be imputed as their “end of study value”). Per protocol analysis will be performed by the a-priori conditions: a) for participants who had high compliance to workout (≥ 2/3 of sessions); b) for participants who had high compliance to diet (≥ score 9 in the Med-diet score and/or caloric consumption change from baseline was not more than 15% of report at baseline); c) for participants who had high compliance to drug therapy (≥80% tablets taken); d) for participants who did not violate the protocol (for example: changed thier habitual diet in the CRT arm; initiated new physical activity other than the one prescrived by us, ect.).

Sensitivity analysis can include all the participants who finished the trial including dropouts, with imputation of the last observation. This will be compared to an analysis which includes only participants that fully completed the study (have an assessment at the end of study).

We may also perform a mixed model for repeated measurements based on assessments of participants who completed the study and had high compliance to the treatment. An unstructured covariance matrix for measurements within the same participant will be employed, assuming that measurements for different participants are independent. The covariates and factors in Table 2 will be nested in the model.

Last, subgroup analysis will be done by stratification to several factors shown in Table 2, where ANCOVA or logistic regression models will be performed according to the outcome assessed (Table 3).

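### The planned subgroup analysis fits models within strata, which does not test whether the treatment effect differs between subgroups, and no interaction test is stated

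*Protocol article*

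**What the plan says.** The subgroup plan is the last sentence of the analysis text (protocol article, Statistical methods, under Baseline comparisons): "subgroup analysis will be done by stratification to several factors shown in Table 2, where ANCOVA or logistic regression models will be performed". The choice between the two model types follows the outcome, as set out in Table 3.

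Table 2, which supplies the stratifying variables, is captioned "List of potential covariates and factors (partial list". Besides treatment it types two entries as factors: GLP-1 agonist use (two levels) and frailty or sarcopenia status (three levels). It types six entries as covariates: baseline weight or BMI, HbA1c, caloric consumption, resting metabolic rate, body fat % and strength.

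The sentence gives no rule for comparing results across strata, and no treatment-by-factor interaction appears elsewhere. The nearest model is the repeated-measures mixed model. It is optional, is limited to compliant completers, and nests the Table 2 terms without describing a test of effect modification.

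On size, the Sample size section states: "For 80% power and significance level of 5% each arm should include 40 subjects". Data handling says that p-values will take account of multiple comparisons by Benjamini-Hochberg, without naming the family. Trial design calls the study exploratory.

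**The concern.** A subgroup analysis asks whether the treatment effect differs between kinds of patient. A model fitted inside one stratum asks whether there is an effect in that stratum. Two such answers, one significant and one not, do not answer the first question, because a difference in significance can come entirely from small numbers and unequal stratum sizes.

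The strata here would be small. With 40 per arm, an even two-way split leaves 20 per arm, and three equal levels of frailty status would leave 40/3 ≈ 13. At that size a treatment that works equally well in everyone will often reach significance in one stratum and miss it in the other. The only formal output the stated method gives a reader is a set of stratum-specific results, so a chance pattern could be reported as effect modification, for example by frailty status or GLP-1 agonist use.

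**Working it through.** **Inputs.** From the Sample size section: 80% power, 5% significance (taken as two-sided; sidedness is not stated), 40 per arm, and a week-10 weight difference of −3.2 kg for empagliflozin against CRT. The second calculation there assumes "body fat % at the end of study will be 37, 36 and 40% for the diet, drug and CRT arms, respectively"; the common SD for that calculation is 6 percentage points. Stratum sizes are not given, so the splits below are assumptions shown as a range.

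**Step 1: the plan's own figure.** The weight calculation states no SD, so 40 per arm cannot be reproduced directly. Solving backwards, SD = 3.2 / [(1.960 + 0.842) × √(2/40)] = 5.11 kg. With SD 5.1 the formula returns 40 per arm and power 0.801. The body-fat calculation gives Cohen f = 0.283, and N = 120 then gives power 0.789. Both agree with roughly 80% power at the stated size, which is all the next steps need.

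**Step 2: power within a stratum under a uniform effect.** The overall standardised effect is 1.960 + 0.842 = 2.802. A stratum holding share *s* of each arm has standardised effect 2.802 × √*s*, and power ≈ Φ(2.802√*s* − 1.960). The SD cancels, so its absence from the document does not matter here.

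- *s* = 0.5: Φ(1.981 − 1.960) = 0.508
- *s* = 0.3 and 0.7: 0.335 and 0.650
- *s* = 0.2 and 0.8: 0.240 and 0.707

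**Step 3: chance that exactly one of two strata is significant.** The strata contain different patients, so P = p₁(1 − p₂) + p₂(1 − p₁).

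- 50/50: 2 × 0.508 × 0.492 = 0.500
- 30/70: 0.335 × 0.350 + 0.650 × 0.665 = 0.549
- 20/80: 0.240 × 0.293 + 0.707 × 0.760 = 0.608

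A t-test version for equal strata also gives 0.500. The three-group ANOVA version gives 2 × 0.466 × 0.534 = 0.498.

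**Step 4: dependence on the size of the common effect** (two equal strata, unadjusted alpha 0.05).

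| Common effect, multiple of design size | Exactly one stratum significant |
|---|---|
| 0 | 2 × 0.05 × 0.95 = 0.095 |
| 0.5 | 0.279 |
| 0.75 | 0.434 |
| 1 | 0.500 |
| 1.25 | 0.422 |
| 1.5 | 0.263 |
| 2 | 0.044 |

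For three equal strata at the design effect, each has power 0.366, and the chance that they do not all agree is 1 − 0.366³ − 0.634³ = 0.696 (0.143 with no effect).

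**Step 5: the comparator.** In 200,000 simulated trials per setting with no true interaction, a treatment-by-stratum interaction test rejected in 0.050 of trials at 0, 0.5, 1 and 1.5 times the design effect.

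**Step 6: stricter alpha as a rough stand-in for Benjamini-Hochberg** (equal strata, design effect): 0.449 at alpha 0.0167 and 0.400 at alpha 0.01.

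**Step 7: power of the interaction test itself.** With two equal strata and SD 5.11 kg, each stratum effect has standard error 5.11 × √(2/20) = 1.62 kg, and their difference 1.62 × √2 = 2.28 kg. A true difference between strata as large as the whole design effect, 3.2 kg, gives 3.2/2.28 = 1.40 and power Φ(1.40 − 1.96) ≈ 0.29.

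**The case against.** The strongest reply is that the faulty inference is not in the document. The sentence says how models will be fitted, not that one significant and one non-significant stratum will be read as a difference. Stratum estimates reported with intervals are legitimate description. This stands, and it is why every discordance rate above is conditional on a decision rule the article does not state.

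A second reply is that a condensed article may leave interaction terms to an analysis plan that is not shown. This stands only in part. The article does not stay silent on subgroups; it fixes a method, and that method does not answer the subgroup question. An unseen plan may add the test, but nothing shown does.

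Third, multiplicity control is planned. It limits false positives among the tests performed and does not add the missing one. Step 6 shows that stricter thresholds reduce the discordance only modestly at the design effect.

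Three stronger readings are tempting, and the documents do not support them:

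- **That about half of all subgroup contrasts without effect modification would look like a difference.** That rate needs a common effect at the design size, two equal strata, unadjusted alpha and the unstated comparison rule. With no treatment effect it is about 10%.
- **That the plan forces cut-points on continuous variables.** The sentence stratifies on factors, and Table 2 types all six continuous entries as covariates. The wording may be loose and the list is marked partial, but no continuous variable is explicitly named for stratification.
- **That every stratum has at most 20 per arm.** The larger stratum of a 30/70 or 20/80 split has 28 or 32 of 40. With the upper recruitment figure ("10% we intend to recruit 120 up to 140 participants") an arm could hold about 140/3 ≈ 47.

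**Conclusion.** The point holds in limited form. The stated subgroup method does not test effect modification, and no interaction test is stated elsewhere in the article. If significance were compared across two strata, a uniform design-size effect would look discordant in about 50% of equal splits, 55% of 30/70 splits and 61% of 20/80 splits, against 5% for an interaction test. These figures assume two-sided unadjusted alpha 0.05, 80% overall power, two-arm comparisons with a normal approximation, and assumed stratum sizes. Away from the design effect the equal-split figure drops, to about 10% with no effect and about 4% at twice the effect.

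The weight is minor. The trial is declared exploratory, neither primary hypothesis depends on subgroups, and no primary or secondary conclusion changes.

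**What to change.** Replace the subgroup sentence with one to this effect: differences in treatment effect between subgroups will be assessed by treatment-by-factor interaction terms in the full-sample ANCOVA or logistic model; any Table 2 covariate examined in this way will be entered as continuous; stratum-specific estimates with confidence intervals will be shown as description only; and a subgroup difference will be claimed only from the interaction.

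With three arms at week 10, the interaction has (3 − 1)(2 − 1) = 2 degrees of freedom for GLP-1 agonist use and (3 − 1)(3 − 1) = 4 for frailty or sarcopenia status. At week 20, with only the diet and drug arms, these become 1 and 2.

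The change costs wording only: no extra patients, visits or data. The real downside is low power. In the example in Step 7, even an interaction as large as the design effect is detected only about 29% of the time, so few subgroup claims will be possible. The report should say so, and should not read a non-significant interaction as evidence that effects are equal.

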## Discussion

Our study aims to evaluate the effectiveness of three different interventions (V-Med diet, CRT and empagliflozin, separately or in combination) on metabolic, anthropometric and physical function parameters in older subjects with T2DM. Several new facets of T2DM treatment in this age group are at the core of this study: 1. This is the first comparison of empagliflozin to lifestyle modification in older patients; 2. This is the first evaluation of a multistage lifestyle and empagliflozin therapy interventions on frailty and sarcopenia; 3. Our hybrid diet intervention (V-Med diet) has thus far not been tested in conjunction to CRT or compared to other treatment modalities; 4.This is the first study to assess the effect of a CRT program in older subjects with T2DM.

There are, however, several limitations to our study protocol: 1) the possibility for volunteer bias which might lead to the inclusion of highly engaged patients. This may affect only the external validity of the study, but not its internal validity; 2) the exclusion criteria include several co-morbidities that are likely prevalent in the older age and associated with diabetes such as recent stroke or myocardial infraction. While this may minimize the generalization of our results, subjects with these conditions may not benefit from our interventions; 3) the apparently narrow HbA1C range used as an inclusion criterion (6.5–8%), may also limit the generalization of our results at this age group. Still, we wish to minimize the effect of major reduction in glycemic values per se (associated with higher values of HbA1C at entry for the study) as a potential contributor to any observed improvements in functional and metabolic states; 4) given its relatively short duration and limited sample size the study is unlikely to evaluate morbidity outcomes such as the incidence of myocardial infraction or stroke.

The combination and comparison of the three interventions for metabolic control may lead to better understanding of their mechanism of action with potential clinical implications in older subjects with T2DM. This study may also provide evidence of the effectiveness of different interventions on the progression from diabetes to sarcopenia and/or frailty and their potential effect on the quality of life older subjects with T2DM.

## Data Availability

Not applicable.

## Abbreviations

30-STS: 30 s Sit To Stand
ABPM: Ambulatory Blood Pressure Monitoring
AE: Adverse event
ANCOVA: Analysis of Covariance
ANOVA: One-way analysis of variance
BIA: Bioelectrical Impedance Analysis
BMI: Body Mass Index
BP: Blood Pressure
CRT: Circuit Resistance Training
DEXA: Dual Energy X-ray Absorptiometry
FM: Fat Mass
FPG: Fasting Plasma Glucose
GLP-1: Glucagon-Like Peptide-1
HbA1c: Hemoglobin A1C
IEMH: Institute of Endocrinology Metabolism and Hypertension
LBM: Lean Body Mass
MedD: Mediterranean Diet
PA: Physical Activity
RCT: Randomized Controlled Trial
RMR: Resting Metabolic Rate
SD: Standard Deviation
SGLT-2: Sodium-Glucose Transporter-2
SMI: Skeletal Muscle Index
SMM: Skeletal Muscle Mass
SMPG: Self-Measured Plasma Glucose
TASMC: Tel Aviv-Sourasky Medical Center
TUG: Time Up and Go test
T2DM: Type 2 Diabetes Mellitus
V-Med diet: Vegeterranean Diet
